## Assignment of interventions: allocation

### Sequence generation {16a}

Not applicable—this is a non-randomized, single-arm intervention study.

### Concealment mechanism {16b}

Not applicable—this is a non-randomized, single-arm intervention study.

### Implementation {16c}

Not applicable—This is a non-randomized, single arm intervention study.

## Assignment of interventions: Blinding

### Who will be blinded {17a}

Not applicable—this is a non-randomized, single-arm intervention study.

### Procedure for unblinding if needed {17b}

Not applicable—this is a non-randomized, single-arm intervention study.

## Data collection and management

### Plans for assessment and collection of outcomes {18a}

After obtaining informed consent, each participant will be assigned a unique study identifier, and then proceed to complete the COST measure. If eligible (i.e., if scoring 22 or less on the COST instrument), participants will then complete the baseline patient experience survey (Additional file 3) and patient outcomes survey. Together these surveys are expected to take less than 30 minutes. Patient outcomes will be assessed using the PROMIS Global Health scale v1.2, PROMIS Emotional Distress-Anxiety – Short Form 6a v1.0, PROMIS Emotional Distress-Depression – Short Form 4a v1.0, and the PROMIS Psychosocial Illness Impact-Positive–Short Form 4a v1.0. The baseline patient experience survey will assess patients’ care-altering behaviors, employment disruption, caregiver cost burden, and the impacts of COVID-19. Following the completion of these surveys, participants will receive an appointment with the financial navigator. During the first FN appointment, financial navigators will complete a comprehensive intake form with the patient (Additional file 4). At all subsequent FN appointments, financial navigators will complete a follow-up check-in form with the patient (Additional file 5). Two to three months after the last FN visit, patients will complete the follow-up survey (Additional file 6), COST measure, and patient outcomes survey. The follow-up survey will include a post-intervention patient experience survey and participant perspectives on FN acceptability (including convenience, accessibility, and satisfaction), responsiveness and alignment with needs, patient-centeredness, and timeliness.

Each site’s financial navigator conducts all study visits with participants. A study flow diagram and study definitions intended to guide navigators through the intervention and administration of surveys and intake forms is included in Additional file 7. For maximal participant convenience and privacy, as well as data completeness, participant surveys and measurements are instructed to be administered by financial navigators via tablets at the time of financial navigation appointments, which may occur in person or via telephone calls. Participant survey data may be entered on tablets or recorded by navigators during follow-up phone calls and then entered in protocol data forms and stored in REDCap afterwards. The baseline, intake forms, check-in forms, and post-intervention participant surveys do not contain any participant identifying information and contain numeric identifiers (study IDs) instead of participant full names.

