### Eligibility criteria {10}

The trial will enroll individuals of all gender identities who are over the age of 18 and have a confirmed cancer diagnosis within the past 5 years or are living with advanced disease. Given the prevalent and indiscriminate nature of FT among oncology patients, we will enroll all cancer types. Participants must read and speak English, plan to continue receiving care at the participating oncology study site, and be willing to complete all study activities. Participants must screen positive for cancer-related financial distress by reporting moderate to severe financial concerns, as measured using the Comprehensive Score of Financial Toxicity (COST measure) (range 0–44, ≤22 defined as eligible) [26, 27]. Patients who report mild or no financial distress will be given educational material that provides basic information about financial resources and the FN program, should they subsequently need it.

Trained financial navigators will deliver the intervention and were selected by each site among individuals meeting the following eligibility criteria: full- or part-time employee of the organization, over the age of 18, and able to read and speak English. Most sites designated individuals already serving in financial counselor or social worker roles to be trained as financial navigators. To ensure that all financial navigators are equipped to conduct the intervention, despite varying levels of experience and training, we will provide 12 h of training, discussed in further detail below.

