#### Patient Outcomes

The primary patient outcome will be change in FT from baseline to follow-up, as measured by pre-/post-intervention completion of the Comprehensive Score for Financial Toxicity (COST) tool. The COST score was selected as the primary outcome given that it has been validated in adult patients with cancer and has been shown to be associated with relevant clinical outcomes (e.g., health-related quality of life) [27]. We will assess mean pre-/post-FN intervention COST scores, which range from 0-44 with a population mean of 22.

Secondary outcomes will include change in HRQoL and change in care-altering behavior. HRQoL will be measured using the PROMIS Global Health Questionnaire, which is a 10-item measure of symptoms, functioning, and HRQoL. We selected this secondary outcome due to the documented negative association between financial burden and HRQoL in the literature [8, 9]. We will assess differences in mean pre-/post-FN intervention HRQoL scores.

Change in care-altering behavior will be operationalized as a dichotomous outcome of forgoing or delaying care due to cost. Harmful, care-altering behavioral responses to the high cost of care, including discontinuation of and non-adherence to medications and delaying or foregoing medical treatment, may contribute to widely observed disparities in cancer mortality by rurality and socioeconomic status [1, 9, 23, 31]. We will assess mean pre-/post-FN intervention differences in the probability of forgoing or delaying care.

Additional patient outcomes will include anxiety, depression, and psychosocial illness impact, all measured using validated PROMIS scales. We will also describe frequencies, proportions, means and standard deviations, as appropriate, of patient-reported post-FN intervention convenience, accessibility, satisfaction, responsiveness (alignment with needs), patient-centeredness, and timeliness. We will use a study-specific patient questionnaire to assess these descriptive outcomes.

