### Recruitment {15}

Patients will be identified by the site staff as potentially eligible for this study based on the study eligibility criteria detailed above, and all eligibility criteria will be verified after approaching patients. Sample recruitment materials are included in Additional file 2. Recruitment of patients will be subject to established protocols defined by UNC and participating institutions. Patients will be recruited by site staff during routine clinic visits to a participating site; therefore, recruitment will not require outreach to patients who are not receiving care currently in the partner oncology sites. Each site will use a combination of passive recruitment (flyers) and active recruitment (staff introduction of the study to the patient if the patient expresses financial concerns). In most cases, staff introducing the study will be financial navigators or social workers. In both active and passive recruitment activities, it will be clear that a patient’s decision regarding participation in the study will not influence the care that they receive. In our pilot study, we were able to recruit 50 participants in four months [32]. As such, we do not anticipate challenges recruiting enough eligible participants to reach the target sample size at each site.

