#### Patient outcomes

We will assess mean pre-/post-FN intervention FT (operationalized as COST scores) using a paired two-sided sample t-test to test the null hypothesis that FN does not result in statistically significant changes in FT, at an alpha level = 0.05. We will again use a paired two-sided sample *t*-test to test the null hypothesis that FN does not result in statistically significant changes in HRQoL, at an alpha level = 0.05. We will use a paired McNemar chi-squared test to test the null hypothesis that the probability of foregoing or delaying care is reduced post-FN is the same as the probability that foregoing or delaying care is increased post-FN.

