## Discussion

The LIFT trial was designed as an individualized, pragmatic, and scalable intervention for cancer patients experiencing FT. It is anticipated that this study will inform and improve the implementation of financial navigation by identifying the critical components and optimum practices associated with addressing the financial needs of cancer patients cared for in both rural and non-rural oncology practices. LIFT seeks to equip stakeholders from various healthcare systems, payers, and financial assistance programs with tools to better coordinate and promote access to financial assistance supportive care and can be delivered flexibly and remotely outside the clinical encounter. Findings from this trial will add to the rapidly developing literature on financial navigation by generating evidence related to its context-specific implementation and effectiveness in diverse oncology practices across the state of North Carolina.

The LIFT protocol should be considered in the context of several limitations. Despite enrolling participants from nine oncology practices representing diverse geographies, sizes, and practice ownership structures, LIFT is limited, at this point, to practices and patients within the state of North Carolina. As such, findings may not be generalizable to the implementation of FN in other states. In this regard, LIFT may have more direct relevance for FN delivered in other states that, like North Carolina, have not expanded Medicaid coverage. As noted above, LIFT was designed as a single-arm study with a pre-post intervention design. As such, this trial will not address the efficacy of LIFT compared to usual care; instead, this trial will address within-person improvement in FT post-program completion. Further, FN, by nature, is tailored to individual patient needs. Consequently, the intensity, length, and specific FN recommendations will vary by patient, which may influence the intervention’s effectiveness in different settings. Finally, FT is not a static problem. The constantly changing nature of health care system ownership, management practices, insurance premiums, and co-pays, coupled with the fluctuating funding capacity of non-profit organizations, underscores the challenges of any intervention targeting an inherently unstable problem.

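### The COST score that admits a patient is also the only pre-navigation value in the primary paired t-test, so regression to the mean can yield a significant gain with no navigation effect

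*Protocol article*

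**What the plan says.** Eligibility criteria {10} sets the entry rule: "COST measure) (range 0–44, ≤22 defined as eligible". Lower scores mean worse financial toxicity. Plans for assessment and collection of outcomes {18a} gives the order of events. The participant consents and completes COST, and then: "If eligible (i.e., if scoring 22 or less on the COST instrument), participants will then complete the baseline patient experience survey". The patient outcomes survey that follows is listed as PROMIS scales only. COST is not repeated before the first navigator appointment, and Table 2 marks COST once before and once after FN. The later score comes at follow-up: "Two to three months after the last FN visit, patients will complete the follow-up survey (Additional file 6), COST measure, and patient outcomes survey".

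Outcomes {12} defines the endpoint: "The primary patient outcome will be change in FT from baseline to follow-up, as measured by pre-/post-intervention completion". It describes the scale as "COST scores, which range from 0-44 with a population mean of 22", so the cut-off equals the quoted population mean. The test is fixed in Statistical methods {20a}: "We will assess mean pre-/post-FN intervention FT (operationalized as COST scores) using a paired two-sided sample t-test", at alpha 0.05, with a null worded as FN not resulting in changes. Section {6b} confirms that there is no comparison group. Recruitment {15} uses flyers and "active recruitment (staff introduction of the study to the patient if the patient expresses financial concerns". The Discussion concedes that there is no comparison with usual care, but adds that "this trial will address within-person improvement in FT post-program completion".

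**The concern.** A score that moves between occasions, through measurement error or real fluctuation, will on average be higher at the next reading in people chosen because their first reading was low. Reusing the selecting score as the baseline puts that expected rise into the primary outcome. The paired t-test compares mean change with zero, so it treats the rise as improvement.

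This differs from the limitation that the authors acknowledge. Trial design {8} and the Discussion accept that the trial cannot compare FN with usual care. Neither mentions regression to the mean, and the within-person change that the Discussion offers instead is the quantity that is biased. A later analysis plan could add an adjustment, but it cannot supply a second pre-FN COST that was never collected.

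At stake is whether a significant primary result can be read as evidence on the stated objective, the effectiveness of FN.

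**Working it through.** **The plan's own figure.** Sample size {14} gives a detectable standardised effect of 0.106 with 700 analysed, 80% power and alpha 0.05. Two-sided: (1.960 + 0.842)/√700 = 2.802/26.46 = 0.106. The two illustrations agree: 1/9.43 = 3/28.29 = 0.106. The sample-size arithmetic is sound.

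**Inputs from the protocol.** Cut-off 22; population mean 22; n = 700; test of zero change; effects from 0.5 to 3.0 points considered.

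**Assumptions not in the protocol.** Between-patient SD (8 to 12), pre/post correlation ρ, mean m of the screened group, bivariate normal scores, and no drift in mean COST without FN.

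**Formulas under no FN effect.** Let a = (22 − m)/SD and λ = φ(a)/Φ(a).
- Expected change = (1 − ρ) × SD × λ
- Variance of change = (1 − ρ)² × SD² × (1 − aλ − λ²) + (1 − ρ²) × SD²
- d = expected change / SD of change
- Probability of a significant gain ≈ 1 − Φ(1.96 − d√700)

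**Worked case, m = 22, SD 10, ρ 0.8.** a = 0 and λ = 0.798. Expected change = 0.2 × 10 × 0.798 = 1.60. Variance = 0.04 × 100 × 0.363 + 0.36 × 100 = 37.45, so the SD of change is 6.12. d = 1.60/6.12 = 0.261 and d√700 = 6.90, so the probability is about 100%. The protocol's 9.43 is not used here. It is an illustrative SD of change, and these assumptions imply 6.12.

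| Screened mean | SD | ρ | Spurious gain | SD of change | d | P(significant gain) |
|---|---|---|---|---|---|---|
| 22 | 10 | 0.9 | 0.80 | 4.40 | 0.181 | 99.8% |
| 22 | 10 | 0.8 | 1.60 | 6.12 | 0.261 | about 100% |
| 22 | 10 | 0.7 | 2.39 | 7.37 | 0.325 | about 100% |
| 18 | 10 | 0.8 | 1.12 | 6.15 | 0.183 | 99.8% |
| 16 | 10 | 0.8 | 0.92 | 6.17 | 0.149 | 98% |
| 14 | 10 | 0.8 | 0.74 | 6.19 | 0.119 | 88% |
| 14 | 8 | 0.95 | 0.12 | 2.52 | 0.046 | 23% |

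The nominal rate in the direction of benefit is 2.5%. At mean 22, SD 8 to 12 and ρ 0.9 to 0.7 give 0.6 to 2.9 points (0.1 × 8 × 0.798 = 0.64; 0.3 × 12 × 0.798 = 2.87).

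**Against the design effect.** With SD 10, the artefact alone reaches d = 0.106 at any ρ below about 0.965 (mean 22), 0.93 (mean 18), 0.90 (mean 16) or 0.84 (mean 14).

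**Bounded scores.** Simulation with scores rounded and held to 0–44 gives similar results: +1.53 points and 100% (mean 22, ρ 0.8), +0.78 and 99.9% (mean 22, ρ 0.9), +0.69 and 89% (mean 14, ρ 0.8).

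**Second baseline.** In the same simulation, a repeat COST with independent measurement error as the pre value brings mean change to about 0 and two-sided rejection to about 5%. If the correlation decays with time, a residual remains. At screened mean 22 it is (r_short − r_long) × SD × 0.798. With r_long 0.7 and SD 10, r_short 0.8 leaves 0.8 points and r_short 0.95 leaves 2.0 of the 2.4 points.

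**Estimating ρ inside the trial.** Among patients at or below 22 (mean 22, SD 10), a true correlation of 0.8 appears as 0.63 because the range is cut. Using 0.63 would give 0.37 × 10 × 0.798 = 2.95 points instead of 1.60. The regression slope of repeat on screening score stays at 0.80.

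**The case against.** The strongest reply is that the size is undocumented. SD, ρ and the screened mean are all assumed, and the recruitment route works against the worst case. If staff approach patients who voice financial concerns, the screened mean probably lies below 22, fewer patients are cut off and the artefact shrinks. That stands. A reader might infer that significance is close to assured whether or not navigation works, but the document does not support this: the mildest case run gives 23%. Nor does it show that recruitment catches a temporary peak in distress. It does not call the concern temporary, and flyers are also used.

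The calculation also assumes a stable mean without FN over up to 6 months of intervention plus 2 to 3 months. The Discussion itself says that financial toxicity is not static. Worsening would offset the artefact and improvement would add to it, so the net bias cannot be determined from the document.

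The pilot's gain of nearly 7 points exceeds the artefact in every scenario run (largest 4.8, at mean 22, SD 12, ρ 0.5). It would therefore be wrong to say that regression to the mean alone would explain a gain of that size.

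Finally, section {26a} speaks of consenting a patient who is interested and eligible, which could hint at an earlier screen. No other pre-FN COST is described, and {18a} places the gating COST after consent. The reuse of the selecting score therefore stands.

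**Conclusion.** The point holds as a statement of what can happen. The eligibility score is the only pre-FN value in a test of zero change with no comparator, so regression to the mean can produce a significant gain when FN has no effect. At SD 10 the spurious gain is 0.8 to 2.4 points for a screened mean of 22 (ρ 0.9 to 0.7) and 0.74 points for a mean of 14 (ρ 0.8). The smallest value run is 0.12 points (mean 14, SD 8, ρ 0.95). The chance of a significant gain runs from 23% to about 100%, against 2.5% nominal. All of this rests on assumed SD, correlation and screened mean, and on no drift.

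A gain near the pilot's would exceed the artefact in these scenarios. The 0.5 to 3 point effects considered in Sample size {14} could not be told apart from it. The open admission of a single-arm design does not cover this, because the bias lies in the within-person change itself.

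**What to change.** 1. For participants still to be enrolled, use the consent-time COST for eligibility only. Repeat COST at the first navigator appointment, before intake, and make the repeat the primary baseline. Preferably do not repeat it on the day of screening: section {11a} offers same-day appointments, and a same-day repeat can leave most of the bias. The amendment should say in advance how participants with and without a repeat enter the primary test.
2. For those already enrolled, report as a sensitivity analysis the mean change against a pre-stated range of expected regression to the mean. Base the range on the COST distribution of all consenters, including those above 22, and on the regression slope of repeat on screening COST or a correlation corrected for range restriction. Do not use the raw correlation among eligible patients, which over-corrects. Consenters are themselves a selected group, and a short-term slope may understate regression over months, so give a range instead of a single value.
3. State that a significant change from the eligibility score is not by itself evidence that FN caused the improvement, and that only change beyond the expected regression is read as compatible with an FN effect.

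Cost: a few minutes per participant at an appointment that already takes place, a small amendment, a smaller apparent effect, and a residual bias of about 0.8 to 2.0 points in the cases shown. Recruitment began in November 2021 and was planned to run to about March 2023. If enrolment has closed, only steps 2 and 3 remain, and without repeat scores the slope in step 2 becomes a stated assumption.

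### The navigator who delivers FN also collects the follow-up outcomes, the instructed occasion for doing so does not exist at follow-up, and no common survey mode is fixed for the two time points

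*Protocol article*

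**What the plan says.** All references are to the protocol article.

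- **Who delivers FN.** Eligibility criteria {10}: "Trained financial navigators will deliver the intervention".
- **Who collects outcomes.** Plans for assessment and collection of outcomes {18a} says that each site's "financial navigator conducts all study visits with participants", and that "participant surveys and measurements are instructed to be administered by financial navigators via tablets at the time of financial navigation appointments". Those appointments may be face to face or by telephone. The next sentence adds that "Participant survey data may be entered on tablets or recorded by navigators during follow-up phone calls".
- **When follow-up falls.** The same section: "Two to three months after the last FN visit, patients will complete the follow-up survey (Additional file 6), COST measure, and patient outcomes survey". Participant timeline {13} also counts the 2 to 3 months from the end of the intervention.
- **When baseline falls.** Section {18a} places COST directly after consent. The other baseline surveys follow for those eligible, and only then is an FN appointment given.
- **What else follow-up contains.** It includes "participant perspectives on FN acceptability (including convenience, accessibility, and satisfaction"), together with responsiveness, patient-centeredness and timeliness.
- **Design and analysis.** There is no comparison group {6b}. The primary outcome is the change in COST {12}, tested by a two-sided paired t-test at 0.05 {20a}.

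**The concern.** There are two separate problems.

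The first is an internal conflict. Surveys are tied to FN appointments, yet the follow-up survey is due well after the last one. For the post-intervention value of the primary outcome, the stated occasion does not exist. Sites are left to choose between a tablet and a navigator's phone call, and no sentence asks them to match what was done at baseline.

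The second is who asks. At baseline the patient has not yet been navigated. At follow-up the patient may be answering the person who has helped for between two weeks and six months. The article itself lists embarrassment and distress when finances are discussed among the likely risks {30}, so answers could plausibly depend on who hears them. With no control arm, a change in reporting cannot be separated from a change in financial toxicity. The limitations in the Discussion concede that there is no usual-care comparison and restrict the claim to change within patients. A reporting shift would weaken that narrower claim too, and it is not mentioned there.

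The patient ratings of FN are a different matter. They are taken once, after FN, and described. They cannot enter the pre/post effect, but they can be too favourable when the person rated collects them. Implementation carries equal weight in this hybrid design {8}, so this is not trivial.

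**Working it through.** **Step 1: can the instruction be met?**

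| Time point | Relation to FN appointments | Survey at an FN appointment? |
|---|---|---|
| Baseline {18a} | before the first appointment is given | not as written |
| Follow-up {18a}, {13} | 2 to 3 months after the last visit or end of intervention | no |

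The tablet-or-phone sentence makes follow-up collection possible. It does not name anyone other than the navigator, and it does not fix one mode for both times.

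**Step 2: reproduce the plan's own figure (Sample size {14}).** Inputs: n = 700 analysed, standardised effect d = 0.106, two-sided alpha 0.05, paired t-test.

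- Noncentral t, df = 699, noncentrality 0.106 × √700: power 79.97%. The plan states 80%, so it is reproduced.
- Both illustrations give the same d: 1/9.43 = 3/28.29 = 0.106.

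The sample size is not in error.

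**Step 3: how small a mean change is significant?** Threshold = t(0.975, 699) × SD/√700.

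- SD 9.43 (the plan's 1-point illustration): about 0.70 points.
- SD 28.29 (its 3-point illustration, three times the SD): 3 × 0.70 = 2.10 points.
- Assumed SD 6 to 12: 0.45 to 0.89 points.

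**Step 4: what would a pure reporting shift do?** Assume no true FN effect and a net shift of b COST points between the two assessments. The document gives no value for b, so a range is shown. Entries are the probability of a significant result.

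| b (points) | SD 6 (assumed) | SD 9.43 (plan) | SD 12 (assumed) |
|---|---|---|---|
| 0.25 | 19.6% | 10.8% | 8.5% |
| 0.5 | 59.6% | 28.8% | 19.6% |
| 0.75 | 91.0% | 55.6% | 37.9% |
| 1.0 | 99.3% | 80.0% | 59.6% |

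The smallest effect considered in {14} is 0.5 points. A shift of that size is within the range the trial treats as an effect. The table shows sensitivity only; it is not an estimate of bias.

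**The case against.** **The conflict is only a wording gap.** The article offers tablet or phone, and the navigators' guide (Additional file 7) and the timeline figure are not shown. This stands in part: follow-up can be done. It does not remove the contradiction in the text, nor the navigator's double role.

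**A reader might infer that baseline is by tablet in clinic and follow-up by phone, so that mode changes systematically.** The documents do not support this. Consent may be taken by phone {26a} with COST straight after it, so baseline may be remote too, and tablet entry is allowed generally. What can be said is that equal mode is not required.

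**A reader might infer that the navigator reads out every question.** Tablet entry may well be self-completion. The article cites privacy and says that patients complete the measures. It does not settle the point.

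**Desirability cancels.** Any tendency to please that is equal at both times drops out of a paired difference. This is correct: only a change matters. The reason to expect one is the relationship built up in between, and neither its direction nor its size is shown.

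**One point is not what the trial is sized on.** Also correct. The trial is sized on d = 0.106, and {14} cites a pilot improvement of nearly 7 points. A 0.70-point shift is 70% of a 1-point change, 23% of a 3-point change and 10% of 7 points. A change as large as the pilot's would not be explained by a small shift. A small positive result would be exposed, and the estimate would be off in either case.

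**Acceptability has other sources.** Practice-level acceptability comes from interviews, and re-contact timing is audited from tracking data. Only the patient-perspective ratings rest on this survey.

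**Changing follow-up alone would create a mode change, and completeness could suffer.** Both points are sound, and the fix below is built around them.

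**Conclusion.** The point holds in a conditional form. Two things are documented: the navigator delivers FN and also administers or records the outcome surveys, and the instructed occasion conflicts with the follow-up timing. A reporting shift would be counted in the primary paired change if it exists. The documents give no evidence that it does, and none of its size.

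Its potential weight rests on n = 700 and an SD of change of 9.43, where an observed change of about 0.70 points reaches significance. The threshold moves in proportion to the SD. The patient ratings of FN may separately be inflated, without effect on the pre/post test.

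The single-arm design, the sample size and the test can all stay as they are. This is a cheap improvement and not a fatal flaw.

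**What to change.** 1. Reconcile the survey-administration paragraph of {18a} with the follow-up timing in {18a} and {13}, and state how the follow-up survey is given once appointments have ended.
2. Have COST and PROMIS self-completed in the same way at baseline and follow-up, by tablet or REDCap link, with answers not seen by the navigator. Because baseline COST decides eligibility, REDCap can display only the eligibility result.
3. Have the FN-experience ratings self-completed and unseen by the navigator.
4. Keep navigator phone collection as a fallback for non-responders. Participants without follow-up data are excluded from the primary analysis {20c}, so completeness must be protected.
5. Record mode and administrator for each COST, and report a sensitivity analysis in pairs with the same mode.
6. Recruitment began in November 2021. For participants already enrolled, keep the baseline mode where possible and report results by mode.
7. Add the navigator's role in outcome collection to the limitations.

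**Cost.** REDCap and the participants' telephone and e-mail details are already in place. The change needs survey set-up and viewing rights, an amendment of a few sentences, two extra data fields, some reminder contacts, and possibly a small loss of response before the fallback call. Same-mode pairs are a selected subset, so that analysis is supportive only.
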